When a person stops using tobacco, the aim of NRT is to replace the nicotine that the smoker would have been receiving, without the additional harmful elements of tobacco.[7]. With fast acting drugs such as nicotine gum, the nicotine is absorbed through buccal mucosa and reaches peak plasma nicotine concentrations within 15–30 min (as compared to within 1–2 min after smoking) and the blood levels reach a flat peak after about 30 minutes of chewing [8]. On the contrary, trans-dermal patches release nicotine more gradually with peak concentrations within hours after application [9]. As a result, none of the available NRT products deliver such high doses of nicotine as quickly as cigarettes. One implication is that combination NRT (fast-acting form + patch) results in approximately 15% to 36% higher long-term quit rates than a single form of NRT. [7]

Using a nicotine replacement treatment (or other smoking cessation drugs) before a quit attempt while smoking normally is called preloading. A systematic review showed limited evidence that nicotine preloading may be effective, but with unexplained heterogeneity between studies. Some studies suggested that nicotine preloading doubled the likelihood of achieving abstinence, while other studies suggested that preloading had no effect [10]. However, more evidence is needed to determine the effectiveness of preloading combination NRT when compared with standard regimen [7]. This study intends to determine and gather further evidence about the effectiveness of preloading combination NRT among adult smokers of Kazakhstan.

**Research question:** What is the effectiveness of preloaded combination nicotine replacement therapy on smoking cessation?

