Carbon monoxide (CO) monitor will be used to assess the exhaled CO level of the study participants during each visit. The cutoff point will be six parts per million or less for nonsmokers and more than six parts per million for smokers [15]. Cotinine is a metabolite of nicotine with a long half-life (15–19 hours) that can be measured in body fluids such as saliva, urine and plasma. Measurement of salivary cotinine as an indicator of tobacco use, exposure to secondhand smoke or use of pharmaceutical nicotine is commonly used in population studies, given the ease of sample collection and minimal discomfort to study subjects.[13]. Hence, saliva cotinine test will be done to assess the smoking status of the participants during baseline and end-line of the study. Saliva cotinine test results will be considered as the biochemical verification for smoking status. However, carbon monoxide levels will be a complementary test to support the evidence for smoking status of the participants. This is because the concentration of cotinine measured in plasma, saliva, or urine has the highest sensitivity and specificity to detect smokers in comparison to CO concentration in blood and expired air due to relatively lower sensitivity than cotinine [14]

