**E. Primary Outcomes:**

The primary clinical outcome will be the binary smoking cessation; abstinence or non-abstinence assessed at 12 months from the starting point of intervention. Non-abstinence will be defined as self-reported smoking anytime during the intervention or follow up and a positive salivary cotinine test.

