**G. Sample size:**

In a study conducted to find the efficacy of preloading combination NRT over standard combination NRT, 6-month sustained abstinence was 47.5% for the intervention group and 27.5% for the control group with a level of significance of 5%, power of 80% in the two-sided test [15.]. This proportion was considered to calculate the sample size for the current study. Eventually, the sample size was derived at 91 in each arm. By considering a loss to follow up of 10% in each arm, the sample size is 100.1 and hence rounded off conveniently to 100 per arm.

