**Results:** The study shall adopt the "Intention to Treat Analysis" mechanism. If the study has missing data more than 10% of the total sample size as expected during sample size calculation, Pattern-Mixture Model within a mixed-effects logistic regression model for longitudinal dichotomous data will be used. Because of the dichotomous outcome, logistic regression version of the mixed-effects model is applicable. The pattern-mixture effects for drug, time, data pattern and their interactions will be interpreted. Pattern mixture sensitivity analysis using SAS/STAT, missing data analysis will be done using R software, and survival analysis will be used to analyze the variation in smoking relapse over time related to the socio-demographics, smoking history, and treatment-related variables.

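### Non-abstinence needs both admitted smoking and a positive cotinine test, so read as written cotinine-positive deniers, and admitted smokers without a positive test, count as abstinent

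*Protocol*

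**What the plan says.** - **Endpoint.** Protocol, section E: "The primary clinical outcome will be the binary smoking cessation; abstinence or non-abstinence assessed at 12 months from the starting point of intervention".
- **Definition.** The same section continues: "Non-abstinence will be defined as self-reported smoking anytime during the intervention or follow up and a positive salivary cotinine test". Abstinence has no definition of its own.
- **Role of cotinine.** Section D: "Saliva cotinine test results will be considered as the biochemical verification for smoking status". Exhaled carbon monoxide is complementary.
- **Properties of cotinine.** Section D: "Cotinine is a metabolite of nicotine with a long half-life (15–19 hours"), and "Measurement of salivary cotinine as an indicator of tobacco use, exposure to secondhand smoke or use of pharmaceutical nicotine" is described as common practice.
- **Test timing.** Sections D and I place the saliva test at the start and the end of the study. The table in section J places it at day 0 and months 3, 6 and 12.
- **Preloading.** Under Background, using treatment "before a quit attempt while smoking normally is called preloading". Section J gives the experimental arm four weeks of this before the quit date.
- **Sample size.** Section G uses six-month sustained abstinence of 47.5% and 27.5%, which leads to 91 per arm. It then reaches 100: "By considering a loss to follow up of 10% in each arm".
- **Missing data.** The Results paragraph after section K: "The study shall adopt the 'Intention to Treat Analysis' mechanism". It calls for a pattern-mixture model if more than 10% of data are missing and gives no rule for 10% or less.

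**The concern.** A test that verifies self-report should be able to overturn a false denial. Under the rule in section E it cannot: a positive test counts only when the participant has already admitted smoking. The rule also lets the absence of a positive test cancel an admission, although cotinine reflects only recent exposure.

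Both errors turn smokers into quitters. If they occur equally in the two arms, quit rates rise in both and the difference shrinks. If they occur unequally, the comparison is biased in favour of the arm with more of them. The result would also not be the sustained abstinence on which the trial was sized, and a participant could count as a relapser in the relapse analysis and as a quitter in the primary analysis.

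**Working it through.** **1. What the rule does.** Taking section E literally, with abstinence as the complement:

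| Self-reported smoking | Positive cotinine test | Class under section E |
|---|---|---|
| Yes | Yes | Non-abstinent |
| Yes | No | Abstinent |
| No | Yes | Abstinent |
| No | No | Abstinent |

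Two of the three rows that carry evidence of smoking are classed as quitting. The third row conflicts directly with the role given to cotinine in section D.

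**2. How far back a test can see.** Five half-lives of 15 to 19 hours are 75 to 95 hours, about 3 to 4 days, after which 1/32 (about 3%) of the level remains. A test at month 12 therefore says nothing about smoking admitted for earlier months.

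**3. The plan's own sample size.** Inputs from section G: p1 = 0.475, p2 = 0.275, two-sided 5%, power 80%. With p̄ = 0.375 and the pooled-variance formula

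n = [1.960·√(2p̄(1−p̄)) + 0.842·√(p1(1−p1) + p2(1−p2))]² / (p1−p2)²

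= [1.960·√0.46875 + 0.842·√0.44875]² / 0.04 = (1.342 + 0.564)² / 0.04 = 90.8, which rounds up to 91 per arm.

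This matches the protocol exactly. The arithmetic of section G is not in question here.

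**4. Effect of misclassification.** Let f be the share of true smokers classed as quitters, equal in both arms. The observed rate is p + f(1−p), so the difference becomes (1−f)·20 points. Power comes from inverting the formula in step 3:

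z = [Δ√n − 1.960·√(2p̄(1−p̄))] / √(p1(1−p1) + p2(1−p2)), power = Φ(z).

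| f (assumed) | Observed rates | Difference | Power at 100/arm | n per arm for 80% |
|---|---|---|---|---|
| 0 | 47.5% vs 27.5% | 20 points | 83.7% | 91 |
| 5% | 50.1% vs 31.1% | 19 points | 78.5% | 104 |
| 10% | 52.8% vs 34.8% | 18 points | 73.1% | 119 |
| 20% | 58.0% vs 42.0% | 16 points | 62.0% | 153 |
| 30% | 63.3% vs 49.3% | 14 points | 51.4% | 196 |

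To read f: if a share d of smokers deny and a share m have no positive test, independently, then f = 1 − (1−d)(1−m). With d = m = 5%, f = 9.75%. With d = m = 10%, f = 19%.

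**5. If f differs between arms.** Take no true effect, with 27.5% abstinent in both arms, and f = 10% in one and 20% in the other. The observed rates are 0.275 + 0.10 × 0.725 = 34.75% and 0.275 + 0.20 × 0.725 = 42.0%. That is a spurious difference of 7.25 points.

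**6. Dependence on the sample size.** Section C gives 490 per arm, not 100. At 490 per arm and f = 20%, z = (0.16·√490 − 1.386) / 0.698 = 3.09, so power is about 99.9%. The power loss in step 4 therefore belongs to the 100 per arm of section G. The shrinkage of the difference and the bias in step 5 do not depend on n.

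**The case against.** **The word *and* may be a loose list of two sufficient conditions.** That is possible, but the text does not say so. The two readings classify every discordant participant in opposite ways, and a primary endpoint cannot rest on that choice.

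**The test is not tied to month 12.** This objection stands in part. A reader might infer that any admitted relapser with a negative month-12 test counts as abstinent. Section E does not date the test, and section J schedules tests at months 3 and 6, so a relapser with a positive month-6 test could already be non-abstinent. If the day-0 test counted, almost everyone would have a positive result and the rule would collapse to self-report alone. How many admitted smokers are lost thus depends on which tests count, which the protocol leaves open. The cotinine-positive denier is misclassified under every dating.

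**Loss to follow-up.** A reader might infer that everyone lost counts as a quitter, because without a test the two conditions cannot both be met. The documents do not support that. The Results paragraph adopts intention to treat and treats absent data as missing, and nothing in the protocol classes a missing outcome as abstinent. A lost participant may also already have an admission and a positive test on record. What remains is narrower: there is no rule when 10% or less is missing, which covers the 10% loss planned in section G. The choice would also matter less than it seems. With 10% loss at 100 per arm, counting the lost as quitters gives 52.8% vs 34.8% (power 73.1%), and counting them as smokers gives 42.8% vs 24.8% (power 77.2%). The difference is 18 points either way.

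**The misclassification rates are invented.** They are assumptions, and so is their equality between arms. The classification error itself does not depend on them.

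**Conclusion.** The definition in section E is wrong as written. It classes cotinine-positive deniers as abstinent, and also admitted smokers with no positive test. It contradicts the verifying role of cotinine in section D and does not match the sustained abstinence used in section G.

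With an assumed, equal misclassification of 10% to 20% of smokers, the planned 20-point difference shrinks to 18 to 16 points, and power at 100 per arm falls from 84% to 73% to 62%. The true rate is unknown, and unequal rates could bias the comparison in either direction. The finding does not extend to a claim that lost participants count as quitters. For them, the protocol simply lacks a rule at or below 10% missing.

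**What to change.** 1. **Define abstinence positively in section E.** For example: a participant is abstinent if there is no self-reported smoking from the quit date to month 12 and a biochemical test at month 12 is negative; a participant who fails either criterion is non-abstinent.
2. **Do not simply replace *and* with *or*.** The present window covers the whole intervention, including the four preload weeks when experimental-arm participants smoke as usual, so *or* would make nearly all of them non-abstinent. An undated positive test would also include day 0, when all participants are smokers.
3. **State which tests count.** Reconcile sections D and I (start and end) with section J (day 0, months 3, 6 and 12). By section D's own account, cotinine also reflects pharmaceutical nicotine. The experimental arm's patch schedule runs 16 weeks, so a month-3 test there cannot separate smoking from treatment.
4. **State how participants without a 12-month outcome are classified.** The rule should be consistent with the intention-to-treat and pattern-mixture approach and should also cover 10% or less missing. Counting the missing as smokers is one option, but it biases against the arm with more loss, so the choice should be deliberate.

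The cost is a short protocol amendment, essentially one sentence for the definition plus the clarifications. Reported quit rates will be lower in both arms than under the present rule.

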**F. Secondary outcomes:**

Secondary outcomes of interest at the final follow-up will include number of quit attempts since enrollment, the number of smoked cigarettes/bidis per day (for those who were not able to quit), duration of use of intervention. The tobacco use outcomes will be smoking excess, smoking reduction, continued use and relapse from the baseline information. Interim smoking cessation outcomes at 3 and 6 months of intervention will be assessed.

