**I. Study tools:**

A semi-structured questionnaire will be developed to capture information about the participants' socio-demographic factors, smoking history, current smoking status, tobacco dependence score, medical history, follow-up of treatment, and stage of transtheoretical model during each visit. The participants will be assessed for carbon monoxide levels, body weight in kg during each visit and salivary cotinine test during the start and end of the follow-up. A pilot study will be conducted on ten participants to test the validity and feasibility of the tools. Processes of change questionnaire, fagerstorm test questionnaire, medication adherence rating scale, and clinician rating scale will be used in the study. Predictors of smoking cessation such as concern about own health, others' health due to passive smoking, smoking expenses, past quit attempts, etc will be measured. [16].

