| Nicotine Replacement Therapy for > 20 cigarettes per day                 | 
Nicotine Patch: Preloading for 4 weeks + 12 weeks post quit date
 
 
- 21 mg: 4 weeks before and after quit date
 
- 14 mg: Next 4 weeks
 
- 7 mg: Last 4 weeks
 
 
Nicotine chewing gums 4 mg for 12 weeks post quit date
(12/day on week 1.....1/day on week 12)
 | 
Nicotine Patch: 12 weeks post quit date
 
 
- 21 mg: 4 weeks after quit date
 
- 14 mg: Next 4 weeks
 
- 7 mg: Last 4 weeks
 
 
Nicotine chewing gums 4 mg for 12 weeks post quit date
(12/day on week 1.....1/day on week 12)
 |
| Nicotine Replacement Therapy for < 20 cigarettes per day                 | 
Nicotine Patch: Preloading for 4 weeks + 12 weeks post quit date
 
 
- 21 mg: 4 weeks before and after quit date
 
- 14 mg: Next 4 weeks
 
- 7 mg: Last 4 weeks
 
 
Nicotine chewing gums 2 mg for 12 weeks post quit date
(12/day on week 1.....1/day on week 12)
 | 
Nicotine Patch: 12 weeks post quit date
 
 
- 21 mg: 4 weeks after quit date
 
- 14 mg: Next 4 weeks
 
- 7 mg: Last 4 weeks
 
 
Nicotine chewing gums 2 mg for 12 weeks post quit date
(12/day on week 1.....1/day on week 12)
 |
| CO monitoring, Fagerstorm score, smoking frequency, medication adherence | 0-day, Month- 1, 3, 6, 9, 12                                                                                                                                                                                                                                                                                                                 | 0-day, Month- 1, 3, 6, 9, 12                                                                                                                                                                                                                                                                             |

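### The month-3 cotinine test falls while the preloading arm is still on nicotine replacement, and the non-abstinence rule counts the smoking that preloading expects

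*Protocol*

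**What the plan says.** Section E times the primary outcome as "assessed at 12 months from the starting point of intervention", and section F says "Interim smoking cessation outcomes at 3 and 6 months of intervention will be assessed". Neither refers to the quit date. Section E defines failure by two conditions: "Non-abstinence will be defined as self-reported smoking anytime during the intervention or follow up and a positive salivary cotinine test".

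The therapy table (section J) gives the experimental arm "Nicotine Patch: Preloading for 4 weeks + 12 weeks post quit date", with gum for the 12 weeks after the quit date. Controls have patch and gum for the 12 weeks after the quit date and no preloading. The Background says that nicotine replacement taken "before a quit attempt while smoking normally is called preloading".

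On verification, section D describes "Measurement of salivary cotinine as an indicator of tobacco use, exposure to secondhand smoke or use of pharmaceutical nicotine" as common practice, then states: "Saliva cotinine test results will be considered as the biochemical verification for smoking status". Exhaled carbon monoxide (CO) is measured at each visit, but section D makes it complementary. The therapy table schedules cotinine on day 0 and at months 3, 6 and 12, and item 4 of the budget justification buys four kits per participant for the same times. Section D elsewhere places the test at baseline and end-line only, and section I has a "salivary cotinine test during the start and end of the follow-up".

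**The concern.** In the experimental arm the start of intervention is not the quit date but 4 weeks before it. A clock that runs from the start therefore brings the month-3 visit inside the treatment period, when a positive cotinine may come from the patch and gum rather than from smoking.

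The non-abstinence rule could normally protect such a participant, because it also requires self-reported smoking. Here it may not. Preloading means using the patch while still smoking, and section E counts smoking at any time during the intervention. On a literal reading, smoking during preloading satisfies the first condition and leaves cotinine to decide alone. Someone who quit on schedule and takes the treatment as prescribed would then be recorded as a failure at month 3.

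**Working it through.** **Inputs.** Treatment schedule: therapy table. Time origin: sections E and F. Cotinine half-life of 15–19 hours: section D. Assumptions: a month is 365.25/12 = 30.44 days, and day 0 is the start of preloading in the experimental arm.

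**Check of the schedule against the budget.** Experimental: 4 + 12 = 16 weeks = 112 days; the budget says 16 weeks and 120 patches. Control: 12 weeks = 84 days; the budget says 12 weeks and 90 patches. The two sources agree.

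**Month 3, experimental arm.** 3 × 30.44 = day 91.3 = week 13.0. Time since quitting: 13.0 − 4 = 9.0 weeks. Treatment left: 112 − 91.3 = 20.7 days = 3.0 weeks. With 4-week months the visit is at week 12 and 4 weeks remain. The arm is on treatment either way.

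**Month 3, control arm.** The protocol does not say when controls quit relative to day 0.

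- Quit on day 0: treatment ends on day 84, so 91.3 − 84 = 7.3 days (175.5 hours) have passed. That is 175.5/19 = 9.2 to 175.5/15 = 11.7 half-lives, and the residue is 0.5^9.2 = 0.17% to 0.5^11.7 = 0.03%. Cotinine is informative in controls but not in the experimental arm, so misclassification under the literal rule favours control.
- Quit at week 4: treatment ends on day 112 in both arms, and cotinine is uninformative in both.

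**Later visits.**

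| Visit | Week | Experimental: weeks since quit | Control, if quit on day 0: weeks since quit | Experimental: weeks since treatment ended |
|---|---|---|---|---|
| Month 6 | 26.1 | 22.1 | 26.1 | 10.1 |
| Month 12 | 52.2 | 48.2 | 52.2 | 36.2 |

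Scheduled treatment has ended in both arms by month 6, so treatment-driven cotinine is a month-3 problem only.

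**Effect of the definition on an experimental participant who quit on schedule, with a treatment-positive cotinine at month 3.**

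- Smoking counted from the start of intervention: both conditions met, scored non-abstinent.
- Smoking counted from the quit date: first condition not met, scored abstinent. Bias zero.

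**The case against.** **The rule needs two conditions.** A quitter who reports no smoking is abstinent whatever the cotinine shows, and it is strained to count permitted pre-quit smoking as failure. This stands as a limit: sensible staff may apply the rule from the quit date. But the text says otherwise, and on the sensible reading a treatment-positive cotinine still verifies nothing.

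**Section E defines the 12-month outcome, and section F does not say that the interim outcomes use the same rule.** True. But section F gives no other rule, and section D makes cotinine the verification of smoking status generally.

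**Sections D and I place cotinine at start and end only.** If they govern, there is no month-3 cotinine and no contamination, but then the section E definition cannot be applied at month 3. The therapy table and the kit budget agree with each other against them. Section D's description of 12 weeks of treatment with a gum-only control also conflicts with the table, which the budget and section 6 (patches and gum in both arms, preloading in the experimental arm) support.

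**Day 0 might be the quit date.** Month 3 would then follow treatment in both arms. That does not match a clock started by the intervention. The timeline allows 365 days after the last recruitment (2023-06-24 to 2024-06-23), where preloading plus 12 months needs 28 + 365 = 393. A planning chart is only weak evidence, however.

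**The contrast between arms is not established.** This stands. Besides the unstated control quit date, a start delay would apply to controls too. If they began 7 days after day 0, their treatment would end on day 91, about 7.5 hours before day 91.3, leaving 0.5^(7.5/15) = 71% to 0.5^(7.5/19) = 76% of their cotinine.

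**Stronger readings.** A reader might infer that the 3-month result will make preloading look harmful. With section G's 47.5% and 27.5% borrowed for month 3, the observed difference is 47.5 × (1 − p) − 27.5, where p is the share of experimental abstainers scored as failures. It runs from +20.0 points at p = 0 to −27.5 at p = 1. The documents do not fix p: they give no cotinine cut-off and no data on positivity late in the taper. A reader might also infer a loss of power for the primary outcome. That needs an assumed rate of positive tests some 36 weeks after treatment, and some of those positives may be real smoking. Finally, the timeline's interim analysis from July 2023 does not say that it covers month-3 efficacy.

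**Conclusion.** The point holds for the month-3 secondary outcome. Under the therapy table, that visit falls about 3.0 weeks before experimental treatment ends, so cotinine cannot verify abstinence in that arm. The literal smoking condition turns this from an uninformative test into a rule that can score successful quitters as failures. Whether it biases the comparison depends on when controls quit: it favours control if they quit on day 0, and verification fails in both arms if they quit at week 4. No magnitude can be derived.

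The primary outcome is affected only through the literal smoking condition, which leaves cotinine to decide alone for anyone who smoked during preloading, and, if controls quit on day 0, through 48.2 versus 52.2 weeks since quitting. The documents do not support calling the primary outcome invalid. The conclusion assumes that day 0 is the start of preloading and that the therapy table and budget govern the treatment and cotinine schedules. The change is worth making before conduct, because analysis cannot recover a specimen taken on treatment.

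**What to change.** 1. Section E: count smoking from the target quit date in both arms, and state that smoking before it does not count.
2. Section D: for anyone using, or scheduled to use, nicotine replacement at a visit, verify by exhaled CO at the section's own cut-off (six ppm or less), not by cotinine.
3. Sections E, F and J: state each arm's target quit date relative to day 0 and count the 3-, 6- and 12-month assessments from it. Take the month-3 cotinine sample at least one week after the last dose. Month 3 is then day 91.3 after quitting, 7.3 days after scheduled treatment ends in either arm.
4. Bring the cotinine schedule in sections D and I into line with the therapy table and budget.

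**Cost.** No extra kits or CO measurements are needed. CO is less sensitive than cotinine, as section D says. The experimental arm's final visit moves by 28 days, to about 2024-07-21 for the last recruit (2024-06-23 + 28 days). Either recruitment closes 28 days earlier (28/450 = 6.2% of the recruitment period) or the reporting chain slips from 2024-12-20 to 2025-01-17, 17 days past project closure. If controls quit on day 0, time since quitting matches between arms but time since randomisation differs by 4 weeks. That is a trade-off to state openly, and it does not require delaying control treatment.
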